This means that patients are not randomized between treatments, but between models of care (PCBH vs. PCBH + GSH). In the extended arm (PCBH + GSH), patients will receive either GSH or BI based on their assessed suitability for GSH treatment. Suitability in this context means that the patient is both interested in and capable of engaging in a self-help treatment and has a primary problem related to mood, anxiety, stress-related conditions, or insomnia. In contrast, the core PCBH arm will include only patients who have received BI. However, within this group, there will be patients would have been suitable for GSH if it was available to them. After data collection is complete, these patients will be retrospectively identified using a standardized procedure that as closely as possible mirrors the extended assessment in the PCBH + GSH model. This approach will allow us to address the secondary research question [2] regarding the subgroup of patients suitable for GSH. The retrospective assessment can determine whether the patient’s primary problem falls within the specified categories and identify any clear indications that they would not be capable of engaging in treatment. However, patient preferences remain unknown, as they were never offered the option. Refer to Table 1 for an overview of the patient groups, along with the codes used to identify them.

**Table 1 Tab1:** Patient groups by randomization, indication for structured interventions, and treatment given

Model of care	Indicated for a structured intervention	Treatment received	Code
**Core PCBH**	Indicated	BI	CORE-I-BI^1^
	Not indicated	BI	CORE-N-BI^2^
**Extended PCBH**	Indicated	GSH	EXT-I-GSH^3^
	Not indicated	BI	EXT–N-BI^4^

^1^Retrospectively indicated for a structured intervention for mood, anxiety, stress-related conditions, or insomnia but received brief interventions (BI)

^2^Retrospectively not indicated for a structured intervention and received brief interventions (BI)

^3^ Assessed by the clinician as indicated for a structured intervention and received guided self-help (GSH)

^4^ Assessed by the clinician as not indicated for a structured intervention and received brief interventions (BI)

Note: In the Core PCBH arm, indication for a structured intervention is assessed retrospectively by an expert rater. In the Extended PCBH arm, indication is assessed in real-time by the regular care clinician

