The clinician is instructed to always use the results of the automated algorithm to inform the focus of the M.I.N.I. interview. As the GSH treatments in this study are possible to use with subclinical problems, the goal of the assessment is not necessarily for the patient to meet a specific diagnosis but rather to pinpoint the problem area most relevant to the patient’s concerns. The diagnostic evaluation concludes with the clinician providing feedback to the patient regarding the assessment results and, when appropriate, offering GSH for the identified condition. If GSH is not a good fit or the patient declines the treatment, they are offered BI. In such cases, BI may be initiated during the first visit if time permits or is otherwise scheduled for a follow-up appointment. Clinicians may also bypass the diagnostic assessment and proceed directly with BI if it is clear from the outset that the patient is unsuitable for GSH. Examples of this are if the patient’s primary concern clearly falls outside the issues addressed by the GSH materials used in this study (for example substance abuse). As in the contextual assessment, patients requiring specialized care will be referred accordingly.

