##### Proportion of patients deemed suitable for GSH

The proportion of patients in the PCBH + GSH arm that are deemed suitable for GSH will be analyzed by both site and clinician. Potential sources of variation will be explored by examining patient characteristics, themes in clinician-reported reasons for not offering GSH to individual patients, and insights from clinician interviews. Retrospective assessments of suitability for structured interventions will also be conducted for patients who underwent extended assessments in practice, allowing for comparisons between the algorithm’s outcomes and real-life assessments.

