For research questions (5) and (6), the analysis groups will be defined based on treatment rather than the model of care. It is therefore essential to clarify how comparison groups are categorized, as they do not align fully with the randomized groups. There is only one subgroup of patients that receive GSH – the patients in the PCBH + GSH arm assessed by the clinician as suitable for GSH (the EXT-I-GSH group). In contrast, patients receiving BI can be divided in several groups, all presented in Table 3. Analyses will be conducted on various combinations of patients receiving BI to account for potential differences among these groups. For example, CORE-N-BI and EXT-N-BI may present with more complex symptoms or social challenges compared to CORE-I-BI – or alternatively, they may have less complex, transient life stressors. Additionally, the diagnostic assessment in the PCBH + GSH model may influence the effectiveness of BI in either direction, necessitating comparisons between patients who received BI in the core model and those in the extended model.

**Table 3 Tab3:** Treatment-level analysis groups

	Core PCBH arm		PCBH + GSH arm	
	CORE-I-BI	CORE-N-BI	EXT-I-GSH	EXT–N-BI
**All patients receiving GSH**			X	
**All patients receiving BI**	X	X		X
**Receiving BI despite an indication for structured treatment**	X			
**Receiving BI in accordance with the indicated treatment**		X		X
**Receiving BI following an extended assessment confirming BI as appropriate**				X
**Receiving BI after the contextual interview**	X	X		

Notes. CORE-I-BI = Patients receiving brief interventions (BI) within the core PCBH model who were retrospectively assessed as suitable for structured treatment

CORE-N-BI = Patients receiving brief interventions (BI) within the core PCBH model who were retrospectively assessed as not suitable for structured treatment

EXT-I-GSH = Patients receiving guided self-help (GSH) after undergoing an extended diagnostic assessment within the PCBH + GSH model, where they were deemed suitable for structured treatment

EXT-N-BI = Patients receiving brief interventions (BI) after an extended diagnostic assessment within the PCBH + GSH model, where they were not deemed suitable for structured treatment

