For research questions (7), (8), and (9), the focus shifts to exploring the feasibility and fidelity of implementing the PCBH + GSH model at scale across multiple PCBH PCCs. To address research question (7), we will examine the proportion of patients who are deemed suitable for GSH following the extended diagnostic assessment. A hierarchical model using a binomial distribution will be used to evaluate whether the suitability rate varies significantly between as well as within centers over time, and to explore any factors contributing to these variations. In research question (8), we will use Hierarchical Linear Models to investigate how patient-related outcomes are affected by interventions and vary across centers and therapists, as well as the factors contributing to these differences. This will help identify potential barriers and facilitators for the successful implementation of both the core and extended PCBH models across different settings. Finally, research question (9) will explore the fidelity of both GSH and BI treatments. Specifically, we will examine how closely clinicians adhere to GSH principles within the PCBH framework, particularly in areas where GSH and PCBH principles may conflict, as well as generally assess the quality of the BI interventions. Fidelity scores will be analyzed descriptively to determine the frequency of low, good-enough and good fidelity ratings. A *t*-test will be used to evaluate whether the mean fidelity score is 3 (good-enough) or higher. Additionally, fidelity will be analyzed across clinicians and PCCs using chi-square tests and logistic regression to identify variability and the factors contributing to it. This will help assess the overall quality of treatment delivery and identify areas that may need further support or adjustment for large-scale implementation.

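### Table 3 labels all of EXT-N-BI as assessed and confirmed for BI, but the group also takes in patients whose assessment was bypassed and patients who declined GSH

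*Protocol article*

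**What the plan says.** Tables 1 and 3 give the extended arm one BI group, EXT-N-BI. The fifth row of Table 3, which is ticked for that group alone, reads "Receiving BI following an extended assessment confirming BI as appropriate". The note under the table describes these patients as receiving BI "after an extended diagnostic assessment within the PCBH + GSH model, where they were not deemed suitable for structured treatment".

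The section Extended diagnostic assessment (Extended PCBH arm) gives three routes to BI. Two are in one sentence: "If GSH is not a good fit or the patient declines the treatment, they are offered BI". The third, for those plainly unsuited to GSH, follows: "Clinicians may also bypass the diagnostic assessment and proceed directly with BI if it is clear from the outset".

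Design and overall procedure speaks to suitability twice. In describing the arms it treats being deemed suitable and accepting GSH as two separate conditions. In explaining the randomization it makes interest in self-help part of what suitability means.

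For research question 7, the Data analysis plan will examine "the proportion of patients who are deemed suitable for GSH following the extended diagnostic assessment", which agrees with the question as listed under Aim and purpose. The measures section says: "The proportion of patients in the PCBH + GSH arm that are deemed suitable for GSH will be analyzed by both site and clinician".

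**The concern.** The Data analysis plan itself stresses that the treatment-level groups must be clearly defined, because they do not match the randomized arms. It also says that the diagnostic assessment might make BI work better or worse, and that BI in the core model must therefore be compared with BI in the extended model. A group labelled as having had the assessment, but containing patients who did not, counts unexposed patients as exposed. A difference, or its absence, could then be credited to an assessment that part of the group never received.

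The same routes matter for question 7. The protocol plans to relate clinician workload to the proportion deemed suitable, and the Discussion expects resource pressure to affect how many patients are offered GSH. If busy clinicians bypass more often, a whole-arm proportion falls, while a proportion among assessed patients need not move. The chosen denominator can therefore change the answer.

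**Working it through.** **Definitions side by side.**

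- *Assessed, GSH not a good fit, given BI.* Meets the Table 3 note and the fifth-row label.
- *Assessment bypassed, given BI.* Meets Table 1, note 4, since the clinician judged the patient not indicated. Fails the Table 3 note and the fifth row, which both require an extended assessment.
- *Offered GSH, declined, given BI.* Not suitable if interest is part of suitability; suitable but not accepting if the two are separate. Even on the first reading, an assessment that ended in an offer of GSH sits badly with the fifth row (BI confirmed as appropriate) and arguably with the fourth (BI as indicated). The third row (BI despite an indication) has no extended-arm entry.

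**Which analyses use the label.** Table 3 serves questions 5 and 6. The main contrast of question 5 is EXT-I-GSH against CORE-I-BI, as is question 2. The first part of question 6 pools all BI patients. None of these depends on the fifth row. The second part of question 6, which compares BI subgroups, does. Question 7 is defined separately and is not computed from Table 3.

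**Size, on assumed rates.** The documents give no bypass, suitability or decline rate, so there is no stated figure to reproduce. Let b be the share of the arm bypassed, s the share of assessed patients found suitable, and d the share of those who decline. As fractions of the arm:

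- receiving GSH = (1 − b) × s × (1 − d)
- EXT-N-BI, N = 1 − (1 − b) × s × (1 − d)
- bypassed share of EXT-N-BI = b / N
- bypassed or declined share = [b + (1 − b) × s × d] / N

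With s = 50%:

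| b | d | N | Bypassed / N | Bypassed or declined / N |
|---|---|---|---|---|
| 10% | 10% | 0.595 | 0.100/0.595 = 17% | 0.145/0.595 = 24% |
| 20% | 20% | 0.680 | 0.200/0.680 = 29% | 0.280/0.680 = 41% |
| 30% | 30% | 0.755 | 0.300/0.755 = 40% | 0.405/0.755 = 54% |
| 10% | 30% | 0.685 | 0.100/0.685 = 15% | 0.235/0.685 = 34% |
| 30% | 10% | 0.685 | 0.300/0.685 = 44% | 0.335/0.685 = 49% |

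The planned total of 983 gives about 490 patients per arm. The middle case then has about 333 in EXT-N-BI: 98 bypassed, 39 declined, 196 assessed and not suitable. A wider grid (b 5–30%, s 50–70%, d 10–30%) puts the bypassed share between 7% and 54%.

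**Dilution.** Suppose the assessment shifts BI outcomes by δ in those who had it and by nothing in those who did not, and the routes are otherwise alike. The group then shows (1 − bypassed share) × δ: 83% of δ at a 17% share and 60% at a 40% share. Decliners do not dilute this contrast, because they were assessed.

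**Question 7, same middle case (b = 20%, s = 50%, d = 20%).**

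- Suitable and accepting, over the arm: 0.8 × 0.5 × 0.8 = 32%
- Suitable and accepting, over assessed: 0.32/0.80 = 40%
- Found suitable, over the arm: 0.8 × 0.5 = 40%
- Found suitable, over assessed: 50%

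**The case against.** Bypass is allowed only when the patient is clearly unsuitable from the outset, so these patients belong on the non-indicated side and satisfy Table 1. What fails is a phrase about a completed assessment, not the four-group scheme. That stands, and it limits the point to Table 3's label and note.

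Decliners can be called not suitable under the definition that includes interest. That also stands as one reading. The sentence separating suitability from acceptance prevents it from settling the matter, and it does nothing for bypassed patients.

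Splitting the group can do harm. The first step of the retrospective assessment sets aside core-arm patients who are clearly not indicated, and they remain in CORE-N-BI. They are the counterparts of bypassed patients. Removing bypassed patients from the extended side alone would create a selection difference. This stands and shapes the fix.

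A reader might infer that the BI comparisons in general are wrong, or that the question 7 rate is wrong. The documents support neither. Most comparisons do not use the affected row. Question 7 agrees with itself in the research question and the analysis plan; the measures sentence names the arm without explicitly stating a denominator. The plan also explores clinicians' reasons for not offering GSH and compares retrospective with real-life assessments. Question 7 is ambiguous, not shown to be in error. A reader might also take 24% to 54% as the mislabelled share, but that counts every decliner as misplaced, which the interest-based definition does not require.

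**Conclusion.** The contradiction is real and lies in the protocol's own text: "Clinicians may also bypass the diagnostic assessment and proceed directly with BI" cannot be squared with a definition under which every EXT-N-BI patient had the assessment. For decliners the text is inconsistent rather than plainly wrong. The effect reaches the fifth row of Table 3, arguably the fourth row for decliners, and the question 6 contrasts meant to show whether the assessment changes BI. The proportion in question 7 needs one stated population and a rule for decliners.

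The size is unknown. Bypassed patients would be about 17% to 40% of EXT-N-BI if half of assessed patients are suitable and the two other rates move together from 10% to 30%, or 15% to 44% if they vary separately over that range. If bypass is rare, the effect is small. Questions 5 to 9 were added during the trial, and the affected contrast is exploratory.

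**What to change.** Before analysis, split EXT-N-BI by route into (a) assessed and not suitable, (b) offered GSH but declined, and (c) assessment bypassed. Use only (a) for the fifth row of Table 3, and amend the note to match. Keep the whole of EXT-N-BI for the core-versus-extended BI contrast, because CORE-N-BI retains the clearly non-indicated patients. Describe that contrast as BI under each model, not as BI with and without a completed assessment.

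For question 7, reconcile the measures section with the research question and the analysis plan: state one denominator and say how decliners count. Report the proportions assessed, found suitable and accepting over all extended-arm patients, so that skipped assessments, clinician judgement and refusal can be told apart.

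The cost is recoding and a revised table, provided the data exist. The protocol mentions clinicians' notes in the CRF, medical records and reasons for not offering GSH, but does not say that bypass or refusal is recorded. Reasons for not offering would not capture a patient who was offered GSH and declined. Where the route cannot be recovered, report it as unknown. The other costs are smaller groups in one exploratory contrast, and a selection difference if (a) alone is ever set against the whole of CORE-N-BI.

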### Aim and purpose

The main purpose of the project is to evaluate if adding GSH as a treatment option within the PCBH framework (PCBH + GSH) – offered only to patients deemed suitable following a brief, structured assessment – can enhance treatment outcomes compared to the core PCBH model. Patient outcomes in the research questions below include everyday functioning (primary outcome) as well as disorder-specific symptoms. The research questions are as follows:

Primary question: When comparing patient outcomes at the care model level after 12 weeks, is PCBH + GSH more effective than the core PCBH model? If not, can non-inferiority of core PCBH be established?Among the subgroup of patients deemed suitable for structured interventions in both groups, do those receiving GSH in PCBH + GSH achieve better outcomes than those receiving BI in core PCBH? Additionally, is this effect more pronounced in patients with conditions expected to require specific treatment components, such as exposure therapy for anxiety disorders, compared to those with conditions like depression and stress, where the benefits of specific treatment components are less clearly established? If not, can non-inferiority of BI be established for these subgroups?Does adding GSH to PCBH increase treatment duration or costs of care delivery? Which model is more cost-effective, considering patient benefits in relation to healthcare and societal costs?Do the care models and treatments differ in patient satisfaction, adverse events, treatment content, and which behavioral changes patients make during and after treatment?Will the protocol-based intervention of GSH decrease variation in treatment outcome compared to BI, especially when comparing patients deemed suitable for structured interventions?In BI, do patients whose therapists use techniques aligned with evidence-based strategies for the patient’s specific symptoms (e.g., exposure for anxiety) achieve better outcomes? How do outcomes differ for various subgroups of patients receiving BI under different conditions, and how do these compare to the group receiving GSH? In GSH, how do therapists’ adherence to treatment protocols impact outcomes? More broadly, how does the specific treatment content, independent of which type of intervention it is provided in, influence patient outcomes?

Additionally, we want to explore if the PCBH + GSH model is feasible for large-scale implementation in healthcare.

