### Power analysis

The power analysis is based on the primary outcome and endpoint, specifically the sum of eight items from WHODAS-12 at FU12. In the pilot trial (manuscript in preparation), a preliminary effect of 0.18 (Cohen’s *d*) was observed between the two care models after eight weeks of treatment. However, at that time, some of the GSH interventions were still ongoing. Many self-help books in the study are structured into 10–12 chapters, completed at a pace of one per week, and many of the studies on the internet-based interventions have a duration of 10–12 weeks [32, 34, 35, 37, 44]. Given this, the endpoint of this full-scale RCT was adjusted to twelve weeks, under the assumption that patients would have finished their treatments, which may produce a somewhat larger effect. A previous trial using similar GSH interventions reported slightly stronger effects [24]. Considering these factors, we estimate an expected between-group effect size of *d* = 0.20. To achieve 80% power with an alpha of 0.05 while accounting for 20% missing data at FU12, a total sample size of 983 patients is required [70]. Recruitment will continue until the power target is reached, with efforts to identify and include new PCCs as necessary. The pilot study (manuscript in preparation) demonstrated an acceptable inclusion rate.

If the primary analysis fails to establish superiority, a secondary analysis will assess whether the core PCBH model is non-inferior to the extended model (PCBH + GSH). No established non-inferiority margin exists for WHODAS-12 in mental health patients in primary care, and even less so for the 8-item version used in this study. Therefore, although not ideal, we reference a previously established non-clinically relevant difference of *d* = 0.24 from a meta-analysis of patients receiving psychological treatment for depression [71]. However, as this threshold is based on disorder-specific measures and treatments, we anticipate that the transdiagnostic WHODAS will be less sensitive to change and will therefore set the non-inferiority margin to *d* = 0.20. To achieve 80% power with an alpha of 0.05, assuming 20% missing data, 775 patients will be required [70]. This falls within the target sample size for the primary analysis. The smaller sample size required for the non-inferiority analysis, despite the identical effect size used, is due to the use of a one-sided test.

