In question (5), the difference in variation of treatment outcomes due to intervention (primarily comparing EXT-I-GSH with CORE-I-BI) will be evaluated by testing if the variation in FU12-scores differs between the two groups using an F-test. To put the difference in variation after treatment in context, the same type of F-test will be made on PRE-scores. The first question in (6) focuses solely on BI and how the therapists’ choice of methods affects outcome. This question requires rating all identified therapeutic methods based on the extent to which they are deemed to have an empirically supported effect for the condition they address. The protocol for these ratings will be developed once all therapeutic methods are identified and prior to exploring their relation to outcomes. The main analysis will be made on all patients receiving BI, regardless of subgroup. The second question in (6) examines potential differences between the subgroups receiving BI. For the third question in (6), only patients receiving GSH will be included, and ratings of therapist adherence will be used to explore its overall relationship to outcomes, as well as for subgroups of patients where GSH manuals with expected specific versus non-specific effects are used. For the final question in (6), relationships between treatment content and outcomes will be explored for all patients, regardless of care model or subgroup.

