The primary statistical methods employed will be Hierarchical Linear Models and Generalized Estimating Equations. Missing data will be handled using multiple imputation techniques that align with the missing data mechanism, while accounting for the multilevel structure of the data. Imputation models will be specified to reflect the underlying data structure, provided the complexity does not hinder model convergence. The analyses will consider the hierarchical structure of the data, such as nesting patients under therapists under PCCs for patient outcomes. The variance of each grouping level in the models will be calculated as the intra-class correlation (ICC) metric. An ICC > 0.10 will be used as a cutoff for the relevance of including it in the final model.

The non-inferiority analysis will be conducted by estimating the mean differences and standard errors at FU12, using Rubin’s rule after performing multiple imputations for missing data. A one-sided 95% CI (corresponding to a 90% two-sided CI) will be calculated for the estimated mean difference. To determine the outcome, we will compare the lower bound of the confidence interval with the non-inferiority margin of *d* = 0.20. If the lower bound of the CI is above this margin, non-inferiority will be established, in line with prior recommendations [72]. For research question (4), which hypothesizes that GSH protocols with assumed specific effects may demonstrate superior outcomes compared to BI, we will include a dummy variable in the model to represent the type of GSH protocol used (specific or non-specific).

For Health Economic Analyses in question (3), effectiveness will be assessed by constructing quality-adjusted life-years (QALYs) based on EQ-5D. Incremental cost-effectiveness ratios (ICERs) will be calculated, and Monte Carlo simulation with non-parametric bootstrapping will be conducted to address the uncertainty of the ICER point estimates. Cost-effectiveness acceptability curves (CEACs) will be employed to examine cost-effectiveness across varying willingness-to-pay scenarios.

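### The two F-tests planned for research question 5 have an error rate that depends on an unstated score distribution, and they cannot attribute a variance difference to the intervention

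*Protocol article*

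**What the plan says.** Aim and purpose poses research question 5: "Will the protocol-based intervention of GSH decrease variation in treatment outcome compared to BI". The Data analysis plan states the target as "the difference in variation of treatment outcomes due to intervention (primarily comparing EXT-I-GSH with CORE-I-BI" and says it "will be evaluated by testing if the variation in FU12-scores differs between the two groups using an F-test". It adds: "To put the difference in variation after treatment in context, the same type of F-test will be made on PRE-scores". It gives no rule for how the PRE result should modify the reading of the FU12 result.

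Three other statements bear on this:

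- The plan says of the treatment-level comparison groups that "they do not align fully with the randomized groups".
- The note to Table 1 says "In the Core PCBH arm, indication for a structured intervention is assessed retrospectively by an expert rater", whereas in the extended arm the treating clinician decides in real time.
- The Data analysis plan says "The analyses will consider the hierarchical structure of the data, such as nesting patients under therapists under PCCs for patient outcomes".

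The text on research question 5 names no scale. The primary outcome is "the sum of eight items from WHODAS-12 at FU12" (Power analysis). No mean, SD, skewness or kurtosis is given for it.

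**The concern.** There are two separate difficulties.

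The first is the error rate. The sampling variance of a sample variance depends on the fourth moment. The F reference distribution assumes the normal value, and the resulting error does not fade as the sample grows. For a bounded sum of items nothing guarantees near-normal kurtosis.

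The second is attribution. The plan wants the part of the variance difference that is due to the intervention. EXT-I-GSH contains patients whom a clinician judged suitable and who accepted GSH. CORE-I-BI contains patients whom an expert rater judged suitable afterwards, with preferences unknown. Two groups chosen in such different ways may differ in spread before treatment. An FU12 test alone cannot separate that from an effect of GSH. A second test at PRE, read beside it, does not estimate whether the FU12 difference exceeds the one already there.

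At stake is the answer to research question 5: it could reflect the shape of the scores or the selection of the groups instead of the treatment.

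**Working it through.** **Plan's own figures.** None is given for research question 5. The sample sizes in Power analysis reproduce: 393 per arm gives 786 / 0.8 = 982.5, rounded up to 983; 310 per arm gives 620 / 0.8 = 775. Neither bears on this point.

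**Check 1: level of the F-test.** Assumptions: integer scores from 0 to 32, equal true variances, group sizes 100/100, 150/200 and 100/250 (the protocol gives no subgroup sizes), 8,000 simulated trials per setting, two-sided nominal 5%. Large-sample formula:

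level = 2 × [1 − Φ(1.96 / √(1 + excess kurtosis / 2))]

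For example, excess kurtosis 0.69 gives 1.96 / √1.345 = 1.69, a level of 9.1%. Excess kurtosis −0.64 gives 1.96 / √0.68 = 2.38, a level of 1.7%.

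| Assumed shape | Skew | Excess kurtosis | Formula | F-test, simulated | Brown-Forsythe, simulated |
|---|---|---|---|---|---|
| Normal (continuous) | 0 | 0 | 5% | 4.9–5.2% | 4.6–5.0% |
| Uniform | 0 | −1.19 | 0.2% | 0.2–0.3% | 4.1–4.8% |
| Beta(2,3) × 32 | 0.29 | −0.64 | 1.7% | 1.8–1.9% | 4.6–4.9% |
| Beta(1.2,2.8) × 32 | 0.65 | −0.31 | 3.3% | 2.6–3.4% | 4.2–5.0% |
| Normal, mean 12, SD 6, rounded and clipped | 0.12 | −0.27 | 3.5% | 3.2–3.7% | 4.7–4.8% |
| Beta(1,4) × 32 | 1.04 | 0.69 | 9.1% | 8.9–9.5% | 4.7–5.0% |
| Beta(0.7,4) × 32 | 1.39 | 1.79 | 15.5% | 14.9–15.6% | 5.0–5.4% |
| Gamma, mean 6, SD 6, clipped | 1.71 | 3.38 | 23.2% | 23.0–23.7% | 4.9–5.3% |

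The level follows kurtosis, not skewness as such, and hardly moves with group size.

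**Check 2: two separate tests against one joint test.** Assumptions: normal scores, so that check 1 plays no part; PRE–FU12 correlation ρ = 0.6; groups of 150/150 and 100/250. The between-group variance ratio is the same at PRE and FU12, so treatment changes nothing. The joint test takes the change in log variance from PRE to FU12 in one group minus that in the other, with

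SE = √[4(1 − ρ²)(1/(n₁−1) + 1/(n₂−1))]

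| Variance ratio at PRE and FU12 | FU12 F-test significant | FU12 significant, PRE not | Joint test significant |
|---|---|---|---|
| 1.00 | 4.8–5.0% | 4.2–4.4% | 4.9–5.0% |
| 1.15 | 12.2–13.8% | 8.6–9.7% | 5.2–5.4% |
| 1.30 | 32.7–35.9% | 17.3–17.8% | 4.8% |
| 1.50 | 65.1–70.4% | 16.8–17.3% | 4.8–5.1% |

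With a persistent ratio of 1.3, about one trial in six shows a significant FU12 test beside a non-significant PRE test although nothing changed. The joint test stays near 5%.

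**The case against.** Several points on the other side are fair.

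- *The score shape is unknown.* A reader might infer that the F-test is known to reject too often because WHODAS scores are skewed. The documents do not support that. Mildly skewed or flat bounded shapes make the test conservative, and the inflated rows need scores piled near zero: beta(1,4) × 32 has a mean of 6.4, and beta(0.7,4) × 32 about 4.8. What stands is that the level is not controlled in either direction.
- *The plan does not claim to test a change in variance.* Research question 5 is worded as a between-group comparison, PRE is context only, and no rule about significance at one time and not the other is written down. This stands as to the wording. But the plan also attributes the difference to the intervention, and that step needs the baseline difference to be taken into account.
- *A baseline variance difference is not shown.* Correct. The protocol also says that the retrospective assessment is built to resemble the clinicians' own. The groups may differ at PRE; no data say that they do.
- *This is a condensed article, and a robust variant may sit in the full analysis plan.* The article does not leave the test open; it names it. The variance-ratio test on unadjusted scores is the natural reading, though the text does not spell that out.
- *A treatment that moves scores towards the floor of a bounded scale also shrinks their variance.* This stands and is not cured by the change proposed here. It limits interpretation under any method.

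**Conclusion.** The point holds in a limited form. The planned F-test has a level that the protocol cannot vouch for: about 0.2% to 24% over the assumed shapes, at any sample size. The PRE test beside it does not justify attributing an FU12 variance difference between non-randomised groups to the intervention. The second limb is the stronger, since it needs no assumption of non-normality; its size depends on the assumed PRE variance ratio, the correlation of 0.6 and the group sizes. A plain two-sample F-test also has no place for the nesting that the plan says its analyses will consider.

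The documents do not show that the test is liberal, that the groups differ in variance at PRE, or that the groups must be redefined. This is an inexpensive improvement to a secondary question added after preregistration. The primary analysis and sample size are untouched.

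**What to change.** Keep EXT-I-GSH against CORE-I-BI as the main comparison and amend the text on research question 5 before analysis:

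1. Replace both F-tests with a variance test robust to non-normality, for example Brown-Forsythe.
2. Base any statement about the intervention on one joint estimate: the FU12-to-PRE variance ratio in EXT-I-GSH divided by that in CORE-I-BI, with a bootstrap confidence interval. Resample patients with their PRE and FU12 scores together, and by cluster if therapist or centre proves relevant under the plan's ICC rule; Brown-Forsythe alone does not deal with nesting.
3. State that a significant FU12 test beside a non-significant PRE test will not be read as evidence of change.
4. State that the joint estimate allows for a variance ratio already present at PRE, but does not make the groups randomised or remove a floor effect.

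Groups formed by the same retrospective rule in both arms can be at most a sensitivity analysis, because some retrospectively indicated patients in the extended arm may have received BI and the question compares treatments received.

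Cost: slightly less power if the scores are truly normal, and modest extra analysis work, mainly combining the bootstrap with the planned multiple imputation. No new data are needed.
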